### Solicited adverse events

Solicited symptoms are adverse events occurring within the seven days follow-up period after vaccination that are inquired about by the investigator or specified designee. Space on the source documents and CRF will be allocated for the recording of solicited symptoms. Table 4 lists the solicited local and general adverse events for the study.

Table 4: Solicited local and general adverse events

|  | **Adverse events** |
| --- | --- |
| **Local (injection site)** | Pain at the injection site |
|  | Swelling at the injection site |
|  | Erythema at the injection site |
| **General** | Fever* (Oral Temperature) |
|  | Gastrointestinal (Nausea) |
|  | Headache |
|  | Malaise |
|  | Myalgia |
|  | Fatigue |
|  | Joint pain |

### Unsolicited adverse events

Unsolicited symptoms are adverse events reported by the subjects which are different from those solicited or solicited symptoms which begin after the seven-day follow-up period for solicited symptoms. Space on the diary cards/source documents and CRF will be allocated for the recording of unsolicited symptoms. Should any systemic (general) signs/symptoms be reported, their relationship with the study vaccine will be assessed by the Investigator and transcribed into the CRF, as described in section 8.3.

## Assessment of intensity

Intensity of the solicited adverse events should be assessed as described in Tables 5-7. Grading of hematological and biochemical laboratory adverse events are in Table 8-9.

Table 5: Intensity grading of local solicited adverse events

| **Adverse event** | **Intensity grade** | **Intensity** |
| --- | --- | --- |
| Pain at injection site | 0 | Absent |
|  | 1 | Mild pain not interfering with function |
|  | 2 | Moderate pain; pain interfering with function but not interfering with activities of daily living (ADL) |
|  | 3 | Severe Pain; pain that severely interferes with ADL |
| Erythema at injection site | | Record greatest surface diameter in mm (see Table 9 ) |
| Swelling at injection site | | Record greatest surface diameter in mm (see Table 9 ) |

Intensity of the general adverse events should be assessed as described in Table 8.

Table 6: Intensity grading of general solicited adverse events

| **Adverse event** | **Intensity grade** | **Intensity** |
| --- | --- | --- |
| Fever (oral temperature  37.5C or 99.5F). | | Record oral temperature in °C/F (see Table ) |
| Headache | 0 | Normal |
|  | 1 | Headache which is easily tolerated |
|  | 2 | Headache that interferes with normal activity |
|  | 3 | Headache that prevents normal activity |
| Fatigue | 0 | Normal |
|  | 1 | Fatigue which is easily tolerated |
|  | 2 | Fatigue that interferes with normal activity |
|  | 3 | Fatigue that prevents normal activity |
| Gastrointestinal | 0 | Normal |
| (*Nausea)* | 1 | GI symptoms which are easily tolerated |
|  | 2 | GI symptoms that interfere with normal activity |
|  | 3 | GI symptoms that prevent normal activity |
| Malaise | 0 | Normal |
|  | 1 | Malaise which is easily tolerated |
|  | 2 | Malaise that interferes with normal activity |
|  | 3 | Malaise that prevents normal activity |
| Myalgia | 0 | Normal |
|  | 1 | Myalgia which is easily tolerated |
|  | 2 | Myalgia that interferes with normal activity |
|  | 3 | Myalgia that prevents normal activity |
| Joint pain | 0 | Normal |
| (> 1 joint) | 1 | Joint pain which is easily tolerated |
|  | 2 | Joint pain that interferes with normal activity |
|  | 3 | Joint pain that prevents normal activity |

Table 7: Intensity grading assigned

| Erythema at injection site | 0 | 0 mm |
| --- | --- | --- |
|  | 1 | > 0 - 20 mm |
|  | 2 | > 20 - 50 mm |
|  | 3 | > 50 mm |
| Swelling at injection site | 0 | 0 mm |
|  | 1 | > 0 - 20 mm |
|  | 2 | > 20 - 50 mm |
|  | 3 | > 50 mm |
| Fever | 0 | < 37.5°C or 99.5°F |
|  | 1 | 37.5 - 38.0°C or 99.5 - 100.4 °F |
|  | 2 | > 38.0 to 39.5°C or 100.4 - 102.2°F |
|  | 3 | > 39.5°C or 102.2°F |

For all other adverse events, maximum intensity should be assigned to one of the following categories:

| 0 | = | No adverse event |
| --- | --- | --- |
| 1 | = | An adverse event that is easily tolerated by the subject, causing minimal discomfort and not interfering with everyday activities. |
| 2 | = | An adverse event that is sufficiently discomforting to interfere with normal everyday activities. |
| 3 | = | An adverse event that prevents normal, everyday activities i.e. prevents attendance at work and necessitates the administration of corrective therapy. |

Table 8: Serum chemistry reference ranges and critical values (Part B, Kenya)

| **Chemistry:** | **Gender** | **Reference Ranges** | **Critical Low** | **Critical High** |
| --- | --- | --- | --- | --- |
| Creatinine (mg/dL): | Male | 0.42 - 1.50 | N/A | >10 |
| (µmol/L): |  | 37 – 133 | N/A | >884 |
| (mg/dL): | Female | 0.17 - 1.17 | N/A | >10 |
| (µmol/L): |  | 15 – 103 | N/A | >884 |
| BUN (mg/dL): |  | 10.0 – 20 | N/A | >120 |
| (µmol/L): |  | 3.6 - 7.1 | N/A | >42.8 |
| ALT (U / L): |  | 0 – 35.0 | N/A | >75.0 |
| AST (U / L): |  | 0 – 35.0 | N/A | >80.0 |
| ALP (U / L): |  | 98 - 279 | N/A | > 800 |
| T - Bilirubin (mg/dL): |  | 0.3 - 1.0 | N/A | >15.0 |
| (µmol/L): |  | 5.0 – 17 | N/A | >257 |
| Sodium (µmol/L): |  | 136 – 145 | <120 | >160 |
| Potassium (µmol/L): |  | 3.5 - 5.0 | <2.8 | >6.5 |
| Bicarbonate (µmol/L): |  | 21 – 30 | <11.0 | >40.0 |
| Chloride (µmol/L): |  | 98 – 106 | <70.0 | >130 |
| Glucose (mg/L): |  | 75 – 115 | <50 | >400 |
| Lactate (mmol/L |  | 0.6 - 1.7 | N/A | >3.4 |
| Total Protein (g / L): |  | 55 – 80 |  |  |
|  |  |  |  |  |
| *Note: The identified values apply to both genders unless otherwise noted* | | | | |

Table 9: Hematology reference ranges and critical values (Part B, Kenya)

| **Hematology:** |  |  |  |  |
| --- | --- | --- | --- | --- |
|  | **Gender** | **Reference Ranges** | **Critical Low** | **Critical High** |
| WBC (x 103 / µL): |  | 3.8 - 10.8 | <2.0 | >40.0 |
| RBC (x 106 / µL): |  | 4.15 - 4.9 | N/A | N/A |
| HGB (g / dL): | Male | 13 – 18 | <8.0 | >20.0 |
|  | Female | 12.0 -16.0 | <7.0 | >20.0 |
| HCT (%): | Male | 42 – 52 | <24 % | >60% |
|  | Female | 37 – 48 | <21.0% | >50% |
| MCV (fL): |  | 86.0 - 98.0 | N/A | N/A |
| MCH (pg): |  | 28.0 - 33.0 | N/A | N/A |
| MCHC (g/dL): |  | 32.0 - 36.0 | N/A | N/A |
| RDW |  | 13.0 - 15.0 | N/A | N/A |
| Platelets (x 103 / µL): |  | 130 – 400 | <81.0 | >1000.0 |
| LY ABS ( (x 103 / µL): |  | 0.85 - 4.1 | N/A | N/A |
|  |  |  |  |  |
| *Note: The identified values apply to both genders unless otherwise noted* | | | | |

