#### Clinical Evaluation

The initial clinical experience with AS01B comes from a study of AS01B-adjuvanted hepatitis B vaccine (personal communication, [name]). In this double blind Phase I/II immunogenicity and safety study in adults, hepatitis B surface antigen (HBsAg) was formulated with AS01B. The HBsAg used in this study is encoded by the same gene as that used to express HBsAg in the RTS,S antigen (which contains both hepatitis and malaria moieties), and the commercially available hepatitis B vaccine (Engerix-B). No SAEs deemed causally related by the investigator to vaccination and no clinically significant abnormal hematological or biochemical laboratory test results have been reported. Most solicited symptoms reported after vaccination with HBsAg/AS01B were not severe in intensity and resolved in the course of the seven-day follow-up period after vaccination. All unsolicited symptoms that were causally related to HBsAg/AS01B vaccination and of intensity Grade 3 (symptoms that prevented normal everyday activity) were local (injection site) adverse events and resolved within two days. In conclusion, HBsAg/AS01B was safe and induced an acceptable amount of reactogenicity.

In the evaluation of immunogenicity, HBsAg/AS01B induced a high and persistent humoral immune response as shown by the presence of seroprotective levels of HBs antibodies 40 weeks after the second dose of vaccine and dramatic boosting of geometric mean titers of anti-HBs antibodies to levels above 900,000 mIU/mL after Dose 3. The cell-mediated immune (CMI) responses to vaccination were characterized by a HBs-specific cytotoxic response, marked lymphoproliferation and IFN-gamma secretion but low interleukin-5 secretion. These CMI results are indicative of a Th1-like immune response and confirm the immunogenicity profile established for the AS01B adjuvant in preclinical studies with RTS,S/AS01B.

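### Injection-site pain that limits daily living less than severely has no grade, and Grade 3 is defined more narrowly for other adverse events than for solicited general symptoms

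*Protocol*

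**What the plan says.** All the grading rules stand in section 8.2 of the protocol (Assessment of intensity).

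- **Injection-site pain (Table 5).** Grade 1 is "Mild pain not interfering with function". Grade 2 is "Moderate pain; pain interfering with function but not interfering with activities of daily living (ADL"). Grade 3 is "Severe Pain; pain that severely interferes with ADL".
- **Headache, fatigue, nausea, malaise, myalgia and joint pain (Table 6).** Easily tolerated is Grade 1, interference with normal activity is Grade 2 and prevention of it is Grade 3. For example, Grade 3 headache is "Headache that prevents normal activity". Therapy plays no part.
- **Erythema, swelling and fever (Table 7).** These are graded by measurement and are not affected by this point.
- **Everything else.** "For all other adverse events, maximum intensity should be assigned to one of the following categories". Grade 2 is "An adverse event that is sufficiently discomforting to interfere with normal everyday activities". Grade 3 opens with prevention of everyday activities and then spells this out, after i.e., as an event that "prevents attendance at work and necessitates the administration of corrective therapy".

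Section 8.1.3 counts a solicited symptom that begins after the seven-day window as unsolicited. Sections 2.2 and 10.2 put the intensity of solicited and of unsolicited symptoms into the co-primary endpoints, and section 10.4.2 has both reported. In section 1.3.2 (Clinical Evaluation), the summary of the HBsAg/AS01B study describes unsolicited events of "Grade 3 (symptoms that prevented normal everyday activity"), again without a therapy condition.

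**The concern.** A graded scale has to give every event exactly one grade, and the same event should get the same grade wherever it is recorded. Table 5 fails the first requirement. The scale for other adverse events, set beside Table 6, fails the second.

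This matters because the tabulated grades are themselves the result. Section 10.3 expects the safety evaluation to be mainly descriptive, so no later modelling step would reveal or absorb inconsistent scoring. Pain was also the most frequent solicited local event in the RTS,S/AS01B trial summarised in section 1.3.2, so the incomplete scale is the one likely to be used most often.

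**Working it through.** The protocol states no figure to reproduce here. The check is to list the possible states and read off the grade that the text gives.

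**Pain, Table 5 (literal text)**

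| State | Grade |
|---|---|
| Does not limit function | 1 |
| Limits function, not daily living | 2 |
| Limits daily living, short of severely | none |
| Severely limits daily living | 3 |

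One of the four ordered states has no grade. Grade 2 excludes it because daily living is affected; Grade 3 excludes it because the effect is not severe.

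**Other adverse events against Table 6 (literal text)**

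| Effect on activity | Therapy judged necessary | Table 6 | Other events |
|---|---|---|---|
| Easily tolerated | either | 1 | 1 |
| Interferes | either | 2 | 2 |
| Prevents | yes | 3 | 3 |
| Prevents | no | 3 | 2 at most |

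The scales differ in the last row only. Events that are Grade 3 on the other-events scale form a subset of those that prevent normal activity, so the Grade 3 count can be equal or lower, never higher. With section 8.1.3, an activity-preventing headache judged not to need therapy is Grade 3 if it starts on Day 2 and not if it starts on Day 10.

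**How many events could be involved.** The documents do not give the share of doses in either affected state, so what follows is illustration only. Group 3 has 20 volunteers × 3 doses = 60 doses.

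- *Pain.* If a share g of doses falls in the ungraded state, 60 × g doses have no grade, or 0.6 doses for each percentage point. For an assumed g of 5% to 10% that is 3 to 6 doses. For scale, the RTS,S/AS01B figures in section 1.3.2 (Table 1) are any pain after 115/142 doses and Grade 3 pain after 4/142. Applied to 60 doses they give 60 × 115/142 = 48.6 and 60 × 4/142 = 1.7.
- *Unsolicited events.* Let p be the share of doses followed by an activity-preventing unsolicited event and q the share of those events judged to need therapy. Expected Grade 3 counts are 60p on the Table 6 standard and 60pq on the literal one. For assumed p of 2% to 10% and q of 25% to 90%, these are 1.2 to 6.0 and 0.3 to 5.4. At p = 5% and q = 50% they are 3.0 and 1.5. The chance of at least one such dose, treating doses as independent, is 1 − 0.95^60 = 95% against 1 − 0.975^60 = 78%.

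**The case against.** Several counter-arguments carry weight.

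- **Assessors can manage.** They may place ungraded pain by the lead words *moderate* and *severe*, and may read the text after i.e. as a gloss on preventing activity. Both are possible. But the definitions attached to the lead words exclude the case, and two defensible readings of a grade are exactly what makes scoring depend on the assessor. The under-count is accordingly a consequence of the literal text and not a demonstrated outcome.
- **Blinding.** The assessors are blinded, so inconsistent scoring should not systematically favour an arm. This stands. It limits the harm to the absolute grades, which are what a descriptive analysis reports.
- **Part A.** A change to Part B alone could break comparability with Part A, whose scale is not shown. This stands and is a cost of the fix.

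A reader might also infer more than the documents support.

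- *That Grade 3 depends on whether therapy was received or accessible.* The text speaks of need; an untreated event can still need therapy.
- *That the holding or stopping rules are distorted.* The symptoms that those rules in section 5.4 name are solicited general symptoms graded by Tables 6 and 7, and the individual stopping rule leaves local reactions to the investigator. The holding rule's symptom list could be read as qualifying only its duration condition, so that other Grade 3 events would count. The text does not settle that, and this point does not rely on it.
- *That comparison with the RTS,S data is lost.* The protocol gives RTS,S Grade 3 counts but no definition of Grade 3 pain. The HBsAg/AS01B description is a brief summary of a scale that is not shown in full.
- *That Grade 3 pain would be inflated about 3 to 4.5 times.* That multiple comes from adding the 3 to 6 assumed doses to the base of 1.7 and scoring all of them as Grade 3. The base is from malaria-naïve adults, while the western Kenya study in section 1.3.2 reports no Grade 3 solicited symptoms.

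**Conclusion.** Both defects are in the wording, and nothing elsewhere in the protocol repairs them. The gap in the pain scale follows directly from Table 5. The mismatch in Grade 3 rests on two readings: that the text after i.e. defines the grade, and that a late-onset solicited symptom is graded with the other adverse events, as section 8.1.3 implies.

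The direction of the second effect is fixed: the unsolicited Grade 3 count is equal to or lower than under the Table 6 standard. The direction of the first is not, since ungraded pain may be scored up or down. The size of either cannot be derived from the documents. This is worth correcting because intensity enters two of the three co-primary endpoints. It does not threaten the validity of the trial.

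**What to change.** In Table 5, reword the pain grades so that they are exhaustive and do not overlap. For other adverse events, reconcile the Grade 3 definition with Table 6. One way is to use the protocol's own *interferes* and *prevents* terms in both places and to turn absence from work and need for therapy into illustrative examples. Corrective treatment stays in its own CRF field, as section 8.1.1 already provides. Which threshold is clinically right is for the sponsor and investigators to settle; the requirement here is that the scales be complete and agree with each other.

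The cost is the wording of two scales and the CRF grading key, and a Grade 3 count that may be slightly higher. The new wording must be checked against the Part A scale before adoption, because the primary objective in sections 2.1 and 10.1 covers both the US and the Kenyan volunteers.

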### Holding Rule for Progression to Next Dose in Part B

- Vaccination with the next dose can be put on hold if five subjects develop a Grade 3 adverse event beginning within two days after vaccination, and persisting at Grade 3 for ≥ 72 hours if the adverse event is malaise, myalgia, fatigue, nausea, fever, headache, or joint pain.

Activation of the Holding Rule requires a thorough review by the Local Medical Monitor in Kenya (Part B, Kisumu, Kenya) and discussion between the investigators, the Medical Monitors, the safety monitoring committee, and Sponsor. Vaccination will restart only if all parties agree to a resumption of vaccination.

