### Stopping Rules

The following Stopping Rules for individual subjects will apply (i.e., the withdrawal of an individual subject from further vaccination):

Stopping Rules:

A. Local Reactions: Investigator discretion

B. Systemic adverse events: Individual subjects will be withdrawn from further vaccination if they develop a Grade 3 adverse event beginning within two days after vaccination, and persisting at Grade 3 for ≥ 72 hours if the adverse event is malaise, myalgia, fatigue, fever, headache, or joint pain.

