**Visits 3-6: Days 1, 2, 3, 7 (3 day) – Post-vaccination 1 follow-up (f/u) visits**

- Recording of solicited and unsolicited symptoms and medication by the health care provider. If Grade 3 AE noted, the PI or other physician investigator must be notified.
- History directed physical exam
- Check of elimination criteria
- Blood collection (Day 7):

**Part B (Kenya):** Approximately 6 mL whole venous blood will be collected for:

- - - Complete blood count (CBC)
    - Serum creatinine, AST,ALT
    - *P. falciparum* antigens detection by HRP 2 and pLDH ELISAs

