### Analysis of safety

**Analysis of reactogenicity**

Reactogenicity analyses will be analyzed as follows.

- The overall percentage of subjects with at least one local adverse event (solicited and unsolicited), with at least one general adverse event (solicited and unsolicited), during the seven-day follow-up period after vaccination will be tabulated.
- The incidence, intensity and relationship of individual solicited symptoms over the 7-day follow‑up period will be calculated per group and vaccine dose.
- The number of subjects with at least one report of an unsolicited adverse event, classified by WHO Preferred terms or by the Medical Dictionary for Regulatory Activities (MedDRA) if available and reported after the Vaccination Phase, will be tabulated per group and vaccine dose. The intensity and relationship to vaccination of the unsolicited symptoms reported will also be assessed. Serious adverse events are expected to be rare, but where observed will be described.

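### Table 7 puts the Grade 2/3 fever boundary at 39.5°C and at 102.2°F, but 102.2°F is 39.0°C, so fevers above 39.0°C and up to 39.5°C carry two grades

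*Protocol*

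**What the plan says.** Fever is a solicited general event (Protocol section 8.1.2, Table 4), and Table 7 in section 8.2 grades it with each limit printed in both units. Grade 0 is "< 37.5°C or 99.5°F". Grade 1 runs from 37.5 to 38.0°C, printed also as 99.5 to 100.4°F. Grade 2 is "> 38.0 to 39.5°C or 100.4 - 102.2°F", and Grade 3 is "> 39.5°C or 102.2°F".

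Table 6 in the same section gives the recording instruction for fever as "Record oral temperature in °C/F", so either unit is allowed. The protocol does not say which scale decides the grade if the two differ, and it gives no other Grade 3 fever limit.

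The grade is used in four places:

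- **Endpoint.** Occurrence and intensity of solicited symptoms is a co-primary endpoint (section 2.2). Section 10.4.2 tabulates by group and dose "The incidence, intensity and relationship of individual solicited symptoms".
- **Notification.** At Visits 3-6 (section 5.5): "If Grade 3 AE noted, the PI or other physician investigator must be notified".
- **Holding rule** (section 5.4). The next dose can be held if "five subjects develop a Grade 3 adverse event beginning within two days after vaccination". Fever is among the events that must also last at least 72 hours at Grade 3.
- **Individual stopping rule** (section 5.4). A subject is withdrawn from further vaccination for a Grade 3 event that starts within two days of vaccination, "persisting at Grade 3 for ≥ 72 hours if the adverse event is malaise, myalgia, fatigue, fever, headache, or joint pain".

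**The concern.** The Celsius and Fahrenheit figures in a row are meant to be the same limit. At the top boundary they differ by half a degree Celsius, so the unit chosen decides whether a fever is moderate or severe.

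Safety and reactogenicity is the primary objective, and Grade 3 is the highest grade in the scale. With 20 subjects planned for the malaria vaccine group, one subject regraded after a given dose moves that dose's Grade 3 fever rate by 1/20, or 5 percentage points. Site staff also act on the grade in real time, so a later correction of the tables would not restore a notification that was not made or a dosing decision already taken.

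**Working it through.** **Inputs.** Fever limits from Table 7; the choice of unit from Table 6; group size and schedule from section 3 (20 subjects, 3 doses); the per-dose fever rate from Table 1 in section 1.3.2.

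**Step 1. Convert every limit**, using F = C × 9/5 + 32 and C = (F − 32) × 5/9.

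| Boundary | Printed °C | Printed °F | °C converted to °F | Agrees? |
| --- | --- | --- | --- | --- |
| Grade 0/1 | 37.5 | 99.5 | 37.5 × 1.8 + 32 = 99.5 | yes |
| Grade 1/2 | 38.0 | 100.4 | 38.0 × 1.8 + 32 = 100.4 | yes |
| Grade 2/3 | 39.5 | 102.2 | 39.5 × 1.8 + 32 = 103.1 | no |

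In the other direction, (102.2 − 32) × 5/9 = 39.0°C. The gap is 0.5°C, or 0.9°F. Since the lower limits convert exactly, rounding does not explain it. Since the same pair stands in both the Grade 2 and Grade 3 rows, a text-extraction fault is unlikely.

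**Step 2. Grade each temperature on both scales**, in steps of 0.1°C from 37.4 to 39.9°C, reading the "greater than" sign of the Grade 3 row as applying to both figures.

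| °C | °F | Celsius grade | Fahrenheit grade |
| --- | --- | --- | --- |
| 39.0 | 102.20 | 2 | 2 |
| 39.1 | 102.38 | 2 | 3 |
| 39.2 | 102.56 | 2 | 3 |
| 39.3 | 102.74 | 2 | 3 |
| 39.4 | 102.92 | 2 | 3 |
| 39.5 | 103.10 | 2 | 3 |

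All other steps get the same grade on both scales. If thermometers read to 0.1 degree (an assumption, as the resolution is not stated), five Celsius readings (39.1 to 39.5) or nine Fahrenheit readings (102.3 to 103.1) carry two grades.

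**Step 3. Bound the number of cases.** Group 3 receives up to 20 × 3 = 60 doses. Table 1 reports fever of any grade after 21 of 142 RTS,S/AS01B doses: 14.8%, 95% CI 9.4 to 21.7. If that rate applied here:

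- point estimate: 0.148 × 60 = 8.9
- lower limit: 0.094 × 60 = 5.6
- upper limit: 0.217 × 60 = 13.0

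That is about 9 fevers of any grade (6 to 13). It is a ceiling on the affected cases, not an estimate of them, because the share in the disputed band is not given.

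**Step 4. Trace the effect on the rules.** For fever, both the holding and the stopping rule need onset within two days and at least 72 hours at Grade 3. The unit changes the outcome only for a fever that stays above 39.0°C for 72 hours without staying above 39.5°C throughout. A hold also needs five subjects.

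**The case against.** The strongest reply is that the ambiguity may never arise in practice. This document covers one Kenyan site, and its other temperature limits, in the exclusion criteria (section 4.3) and the deferral rules (section 4.4.1), are in Celsius only. If the site records in Celsius throughout, 39.5°C applies to everyone and no subject gets two grades. That is plausible, but it is an inference. It also leaves open which figure was intended. If it was 39.0°C, a Celsius-only site would grade every fever from 39.1 to 39.5°C one level too low.

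Other points on impact largely stand:

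- The western Kenyan study of 255 adults summarised in section 1.3.2 reports no vaccine-related Grade 3 solicited symptoms, and the fever footnote to Table 1 reports no Grade 3 events. Neither study's fever cut-offs are given, but both suggest few cases, possibly none.
- Section 8.1.1 has the investigator evaluate all adverse events at each visit, so a fever in the band still reaches an investigator, though perhaps less promptly.
- A subject who is febrile at a scheduled dose is deferred at 37.5°C whatever the grade.
- The holding rule is permissive and leads to a review. Only the individual stopping rule acts automatically.
- The safety analysis is expected to be descriptive (section 10.3), and grades can be re-derived from recorded temperatures.

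It is also true that the Fahrenheit column prints 100.4 in both the Grade 1 and Grade 2 ranges, whereas the Celsius column separates them. That is a trivial overlap at a single reading.

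These points limit the consequences. They do not make the two limits agree.

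**Conclusion.** The concern holds: the Grade 2/3 fever boundary is wrong as written, in both rows where it appears. The conflict covers temperatures above 39.0°C up to and including 39.5°C (above 102.2°F up to 103.1°F). The conversion rests on no assumption beyond reading the "greater than" sign as applying to both units.

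The practical effect is probably small. The ceiling of about 9 fevers assumes that the per-dose rate from malaria-naïve adults given a different antigen carries over, and only part of those would fall in the band. The effect on holding and stopping is confined to sustained fevers of a narrow kind. The point should still be fixed, because site staff apply this threshold in real time, it feeds a co-primary endpoint, and the document does not show which value was meant.

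**What to change.** The sponsor's clinicians should choose the intended boundary and print it consistently in the Grade 2 and Grade 3 rows of Table 7:

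- keep 39.5°C and change 102.2°F to 103.1°F, or
- keep 102.2°F and change 39.5°C to 39.0°C.

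Either choice makes the two scales agree. Two optional additions: have the CRF record temperature in one unit only, and start the Fahrenheit Grade 2 range above 100.4 so that it matches the Celsius column. The cost is one boundary value corrected in two table rows. Design, sample size and procedures do not change.
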